### Control Group

The control cohort recruited during the development of the app receives usual care with no access to the RESPONSE system. Data collection for the control group commenced in January 2020 but was interrupted and paused because of COVID-19 for several months and is ongoing; recruitment will continue until the app is released and tested prior to commencing the trial.

### Intervention group

Intervention participants will receive usual care, supplemented by symptom monitoring through completion of SSPedi, stratified alerts based upon the pre-defined algorithms, access to symptom management recommendations and graphical displays of symptom trends over time through the RESPONSE system (Fig. 1). Recruitment will continue until 1:1 matching is achieved on disease type of the recruited controls.

### Procedures

All participants complete the SSPedi ePROM at the start of a treatment cycle weekly for eight weeks, along with other validated measures. Control group participants complete all measures, including SSPedi through REDCap™ and receive up to three reminders sent via email or text message. Intervention participants complete SSPedi using the mobile RESPONSE app, reminders pop-up notifications occur at 24 and 48 h if SSPedi is missed. The dashboard is used to schedule SSpedi timing and the reminder notifications. Other validated measures in the intervention group are collected via REDCap™ [38]..

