### Inclusion criteria

Children aged 4 to 18 years, receiving active treatment for blood cancer or solid tumors and their caregiver/s are included. Active treatment for cancer is defined as receiving either planned cycles of chemotherapy or radiotherapy. Participants will be recruited within two weeks of a planned treatment cycle. Prior to recruitment, their clinical status and the appropriateness of approaching potential participants will be confirmed with the treating clinicians. Participants are required to be able to read and understand English, and to have access to a smartphone, iPad or computer and Internet.

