### Sample size

The sample size is based upon feasibility. Considering previous research [37], we anticipate 50 % of participants will meet the eligibility criteria (many children diagnosed with cancer are aged under 4 years) and that 80 % will consent to the study, meaning over a 12-month time period, approximately 80 participants per group can be recruited. To account for 20 % attrition, recruitment will continue until there are 96 participants in each group. In terms of clinical effectiveness, a difference of 2.7 on the SSPedi scale is considered clinically meaningful at the individual level [24]. Data from this current study will be used to calculate a sample size powered to detect clinically meaningful differences in a larger future study.

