### Effectiveness outcomes and evaluation

The primary outcome is total symptom burden measured by weekly completion of SSPedi by the child participant, caregiver proxy or child and caregiver co-completion. Secondary outcomes include health-related quality-of-life (PedsQL Cancer Module) [39], the Pediatric Distress Thermometer [40], and FACES pain scale [41]; these measures are collected at baseline, weeks four and eight post-baseline again by the child participant, caregiver proxy or child and caregiver co-completion. The PedsQL Cancer Module is a validated tool with 32 items for cancer specific health related Quality of Life measurement in children and adolescents aged 2–18 years (child and caregiver proxy) [39]. The Pediatric Distress Thermometer is a one item screening tool that measures distress, defined as worry, anxiety, sadness, or fear, reported by the child on a visual analogue scale from 0 (no distress) to 10 (severe distress), based on the child’s experience in the previous week [40]. A recent study has identified threshold scores for children with cancer [42]. The FACES pain scale also uses a visual analogue scale to assess intensity of pain and is validated from age 4 years onwards (and caregiver proxy). The FACES pain scale conforms to a linear interval scale from 1 to 10 scale [41].

Data collected regarding the child includes gender, age at diagnosis, age at study enrolment, diagnosis, treatment, and complications during the study period; all of which will be collected from medical records.

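### The app is the only stated route for the intervention group's SSPedi, so stopping the app ends the treatment and the primary outcome together

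*Protocol article*

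**What the plan says.** The article's Effectiveness outcomes section defines the endpoint: "The primary outcome is total symptom burden measured by weekly completion of SSPedi by the child participant, caregiver proxy or child and caregiver co-completion".

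The Procedures section assigns collection routes by group.
- **Control:** "Control group participants complete all measures, including SSPedi through REDCap". These families "receive up to three reminders sent via email or text message".
- **Intervention, SSPedi:** "Intervention participants complete SSPedi using the mobile RESPONSE app", and "reminders pop-up notifications occur at 24 and 48 h if SSPedi is missed".
- **Intervention, everything else:** "Other validated measures in the intervention group are collected via REDCap".

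Under Mobile Application Design, the traffic-light alert is worked out once SSPedi has been completed, and the advice is then shown inside the app.

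The Inclusion criteria require families "to have access to a smartphone, iPad or computer and Internet". The Sample size section allows for 20% attrition: "recruitment will continue until there are 96 participants in each group".

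The Effectiveness analysis section plans linear mixed-effects models, a description of missing data, imputation of data missing at random, and a sensitivity analysis for bias from missing data.

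**The concern.** SSPedi in the app is both the first step of the intervention and the measurement of the primary outcome. A family that removes the app, ignores its notifications or finds it a burden stops receiving alerts and advice, and as written its weekly SSPedi stops too. REDCap still reaches that family for quality of life, distress and pain at weeks 4 and 8, but not for the primary outcome. A control family has no app to abandon, and its SSPedi and reminders stay on REDCap, email and text.

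This is separate from any difference in how families answer on an app compared with a web form. If the two modes gave identical scores, the problem would remain.

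The hypothesis concerns putting the system into practice, in a trial described as pragmatic. That calls for the outcomes of everyone offered the app. If on-app scores are all there is, the comparison moves towards continuing users against all responding controls.

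There is also a wording mismatch. A family whose only device is a computer meets the device criterion. As a control it can give every SSPedi; in the intervention group it would need a mobile app.

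**Working it through.** **1. The plan's own attrition figure.** 80 × 1.20 = 96 per group, as stated. This allowance replaces numbers; it does not recover the scores of families who stop. The same 20% is applied to each group. It is a general attrition figure, not a forecast of app stopping.

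**2. What the analysis would do with stoppers.** Every SSPedi score in the intervention group comes from a family using the app that week. A mixed model or missing-at-random imputation built on those scores predicts a stopper as if still on the app. The error per stopper is d, the true SSPedi minus the model's prediction.

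**3. Bias in the comparison.** With p the share stopped by week 8, I for intervention and C for control:

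Overstatement of benefit = p_I × d_I − p_C × d_C

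The documents give no value for d. I assume 2 to 5 points, equal in both groups.

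| Stopped, intervention / control | Calculation | Bias at week 8 (points) |
|---|---|---|
| 20% / 20% | 0.20d − 0.20d | 0 |
| 20% / 10% | 0.10 × 2 to 0.10 × 5 | 0.2 to 0.5 |
| 20% / 0% | 0.20 × 2 to 0.20 × 5 | 0.4 to 1.0 |

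**4. Averaged over eight weeks.** Stoppers contribute scores until they stop. If stopping accrues evenly, the share stopped by week k is p × k/8, and its mean over weeks 1 to 8 is p × 36/64 = 0.5625p. With d constant, 0.2 to 0.5 becomes 0.11 to 0.28, and 0.4 to 1.0 becomes 0.23 to 0.56.

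**5. Sign.** If families stop because the child is well, d is negative. At 20% versus 10% with d of −2 to −5, the bias is −0.2 to −0.5, which understates the benefit.

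**6. Equal d is a special case.** d_I also contains any app benefit lost on stopping, which d_C cannot. Illustration only: suppose the app lowers SSPedi by 2.7 while used and by nothing afterwards, and stoppers in both groups are otherwise as predicted. Then d_I = 2.7 and d_C = 0. At 20% stopping the effect over all families is 2.7 × 0.80 = 2.16, the on-app data show 2.7, and the gap is 0.54. The plan states no expected effect, so 2.7 is borrowed here.

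**7. Rough reference.** Against the article's 2.7 points, 0.2 to 0.5 is 7% to 19% and 0.4 to 1.0 is 15% to 37%. The article calls 2.7 meaningful for an individual, so it is not a yardstick for a difference in group means.

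**8. Is non-completion foreseeable?** Implementation counts as successful on completion if more than half of intervention families give 80% of their SSPedi. 0.8 × 8 = 6.4, so 7 of 8 are needed. With 41 of 80 families giving 7 and the rest none, 41 × 7 / 640 = 45% of scheduled forms would still pass.

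**The case against.** Several points on the other side are sound.

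- A reader might infer that SSPedi cannot be given outside the app. The article does not say so. It names one route and sends the other measures elsewhere. It is a condensed account, and the full protocol may hold a fallback.
- A reader might infer that only the intervention group loses data. That is not supported. A child too unwell to answer can miss REDCap forms as well, attrition is allowed for in both groups, and the Limitations section says only that more than half of controls had completed over 80% of measures.
- A reader might infer that the plan overlooks missing-data bias. It does not: it plans to describe missingness and to run a sensitivity analysis, whose details may be left to the analysis plan.
- Week 4 and week 8 REDCap measures, where answered, are information after stopping that could inform imputation. They are not SSPedi.
- The staff portal lets non-completers be seen. That is tracking, not a second way to answer.
- Nothing in the document removes stoppers from their group.
- The trial is non-randomised, sized by feasibility and meant to inform a larger one.

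These points limit the size and certainty of the bias. They do not remove the structural link: as written, leaving the app ends treatment and endpoint together in one group, and no comparable link exists in the other.

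**Conclusion.** The point holds as a design weakness worth correcting. In the intervention group the only stated SSPedi route is the app that delivers the treatment, so missing primary outcomes are tied to stopping treatment; in controls they are not. The planned analyses can describe this uncertainty but cannot supply the missing scores.

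The size is not fixed by the documents. With equal d of 2 to 5 points, the week-8 bias runs from nil (20% stopping in both groups) through 0.2 to 0.5 points (20% versus 10%) to 0.4 to 1.0 points in the extreme case where all 20% falls in the intervention group. It is roughly half that averaged over eight weeks if stopping is evenly spread. Stopping shares by group and d are assumptions. It would be wrong to conclude that the benefit is certain to be overstated, since the sign depends on why families stop.

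The number of computer-only families is not given and is probably small. That part is a mismatch between two sections to be reconciled.

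**What to change.** 1. **Procedures.** State that when an intervention family stops the app, or a weekly SSPedi is still missing after the 48 h reminder, SSPedi is requested through the REDCap link the family already uses, through to week 8. Flag the route of each score and record the date of last app use. Count app completions separately, so that the completion criterion under Implementation Analysis still measures use of the app.
2. **Effectiveness analysis.** State that SSPedi given in REDCap by stoppers enters the primary analysis in the intervention group.
3. **Inclusion criteria.** Reconcile device access with the mobile app and apply the same device requirement to both groups. For controls already enrolled, record the device and add a sensitivity analysis that leaves out computer-only families.

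If the full protocol already has a fallback route, citing it in Procedures would settle item 1.

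The cost is a few sentences and one more REDCap form for families who already use that system. The Control Group section says controls are recruited until the app is released and tested, before the trial starts, so on the article's account intervention procedures could still be changed. There are two downsides: collection routes become mixed within the intervention group, and SSPedi given in REDCap does not trigger the in-app alert.

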### Effectiveness outcomes and evaluation

The primary outcome is total symptom burden measured by weekly completion of SSPedi by the child participant, caregiver proxy or child and caregiver co-completion. Secondary outcomes include health-related quality-of-life (PedsQL Cancer Module) [39], the Pediatric Distress Thermometer [40], and FACES pain scale [41]; these measures are collected at baseline, weeks four and eight post-baseline again by the child participant, caregiver proxy or child and caregiver co-completion. The PedsQL Cancer Module is a validated tool with 32 items for cancer specific health related Quality of Life measurement in children and adolescents aged 2–18 years (child and caregiver proxy) [39]. The Pediatric Distress Thermometer is a one item screening tool that measures distress, defined as worry, anxiety, sadness, or fear, reported by the child on a visual analogue scale from 0 (no distress) to 10 (severe distress), based on the child’s experience in the previous week [40]. A recent study has identified threshold scores for children with cancer [42]. The FACES pain scale also uses a visual analogue scale to assess intensity of pain and is validated from age 4 years onwards (and caregiver proxy). The FACES pain scale conforms to a linear interval scale from 1 to 10 scale [41].

Data collected regarding the child includes gender, age at diagnosis, age at study enrolment, diagnosis, treatment, and complications during the study period; all of which will be collected from medical records.

### Effectiveness analysis

Changes in the primary outcome of total symptom burden between the intervention and control group will be descriptively reported and examined using mixed linear mixed-effects models accounting for repeated observations from the same child. Secondary outcomes of quality of life, distress and pain will also be examined with mixed effects regression. This will allow for exploration of effects both within and between individuals, as well as the intervention and control groups. Potentially confounding co-variables will be included, particularly if any demographic or clinical differences are identified between groups at baseline. Outcomes will be stratified by the person completing the measures (caregiver, child participant or co-completion) and gender to determine whether effects differ based upon these factors. A sensitivity analysis will also be conducted, where possible, to compare results between caregiver versus child participant report [43]. The amount and types of missing data will be descriptively reported. Missing data at random will be imputed, and a sensitivity analysis will be completed to investigate possible sources of bias due to missing data. The characteristics of symptom burden over the eight-week study duration, as well as any pharmacological or non-pharmacological interventions or referrals provided to address symptoms will be described. Quantitative data analysis will be undertaken with IMB SPSS version 26.0, Released 2019, Armonk, NY:

### Implementation outcomes and evaluation

Outcome measures for elements of RE-AIM/PRISM [44] includes data from the RESPONSE app, stakeholder and participant interviews and health service administrative data. To provide preliminary data regarding the cost effectiveness of the intervention an economic evaluation will compare healthcare utilisation between groups, and fixed and variable costs of the intervention to the health service.

Implementation evaluation of the RESPONSE app will be determined by data including the behaviour of users (frequency of app use, completion of SSPedi, activation of alerts). Participants will be asked to keep a log diary of any technical difficulties encountered. The feasibility, acceptability and safety of the RESPONSE app will be explored in semi-structured interviews with a subset of recruited child participants, caregivers and clinicians. Fidelity of the intervention will be assessed through study records.

### Implementation Analysis

Review of logged data will provide information regarding the ability of the RESPONSE system to capture symptom burden, completion rates of the SSPedi tool, generation of stratified alerts, access of symptom management recommendations and review of graphical displays. Each event on the app will be collected, so that the total count of events can be calculated over the study time frame. Data analysis will be undertaken per participant as well as across the whole study and across a specific time frame (e.g. one day). Reliability of the RESPONSE system to provide appropriate care management recommendations based on symptom scores will be evaluated with test-retest reliability (intraclass correlation coefficients for repeated measures within the same person) between consecutive days.

Process evaluation will consider causal pathways, safety aspects and mechanisms influencing implementation into clinical practice. Experiences of the intervention from both participants’ and clinicians’ perspectives will assess feasibility, appropriateness, acceptability, and satisfaction with the RESPONSE system for symptom management. Qualitative data will be analysed using interpretive description, an inductive analytical approach to understand clinical phenomena that yield applications implications [45]. Finally, Framework analysis [46] will be used for quantitative and qualitative data. These data will be mapped to the constructs of RE-AIM as overarching themes in matrices, where columns are codes and rows are participants [46]. Positive and negative quotes and descriptive data will be examined for each construct in the RE-AIM framework to determine influences on implementation. NVivo (released in March 2020) [47] will be used to manage qualitative data analysis. Successful implementation is defined a priori as:

> 50 % of intervention participants completing 80 % of scheduled SSPedi measures.> 50 % of intervention participants acting appropriately upon alerts to contact clinical teams.> 50 % of intervention participants accessing relevant symptom management advice.> 50 % of intervention participants discussing RESPONSE data in clinical consultations..

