Accordingly, we report the protocol of a study to evaluate the effectiveness and implementation outcomes of an ePROM intervention targeting symptoms in children undergoing systemic cancer treatment – the RESPONSE system. The intervention involves multiple components including: (1) weekly monitoring of symptoms using a validated, child friendly ePROM (SSPedi) [24, 25]; (2) stratified alerts for symptoms that reach pre-determined thresholds requiring intervention; (3) evidence-based symptom management recommendations, and (4) graphical displays of SSPedi information enabling symptom trends to be visualised over time. The comparison intervention involves completion of ePROMs alone, without stratified alerts, symptom management recommendation or graphical displays.

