### Stratified alerts, symptom management recommendations and graphical trends

The clinical reference group iteratively developed algorithms to determine thresholds for each of the 15 symptoms measured by SSPedi. Each symptom was individually appraised for the level of potential risk, with each possible answer of bother determining one of three responses regarding management. The algorithms include reference to previous SSPedi completion within the previous 14 days, as well as diagnosis. The final algorithms were ratified by oncologists, nursing and allied health staff at the children’s cancer centre.

Evidence-based symptom self-management recommendations were drafted from clinical practice guidelines (where available) by the clinical reference group and endorsed by medical, nursing and allied health oncology clinicians working in the study setting [28]. Recommendations were appraised for ease of reading, ensuring content was at an appropriate reading level (grade 8) or below. Wording was also reviewed by two adolescents (age 13 and 15 years) for content and language resulting in some changes. A consensus was obtained through discussion with the clinical reference group to graph SSPedi both for one-time completion (visualising all symptoms on a bar graph), as well as an option to select up to three symptoms to view over a 1-week, 4-week and 12-week time period. These time periods were chosen to correspond with common chemotherapy protocols in children’s cancer. All components were then incorporated into the design of a mobile application (app).

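### The consecutive-day test-retest ICC has no scheduled data under a weekly SSPedi design, and it measures symptom stability rather than whether the system's recommendations are correct

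*Protocol article*

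**What the plan says.** The Implementation Analysis section of the protocol article fixes both the claim and the statistic. The claim: "Reliability of the RESPONSE system to provide appropriate care management recommendations based on symptom scores will be evaluated with test-retest reliability". The statistic and retest interval: "intraclass correlation coefficients for repeated measures within the same person) between consecutive days".

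The schedule is given in several places, always as weekly:

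- Background lists as an intervention component "weekly monitoring of symptoms using a validated, child friendly ePROM".
- Procedures: "All participants complete the SSPedi ePROM at the start of a treatment cycle weekly for eight weeks".
- Effectiveness outcomes and evaluation: "The primary outcome is total symptom burden measured by weekly completion of SSPedi".
- Table 3 gives the same frequency for the primary outcome.

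In the intervention group, "reminders pop-up notifications occur at 24 and 48 h if SSPedi is missed". No section describes daily completion, a next-day repeat or a retest subsample.

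Two further facts bear on the point. The section on development of the intervention says that SSPedi asks about bother on the current or the preceding day. The section on stratified alerts says that each answer leads by rule to one of three management responses, and adds: "The algorithms include reference to previous SSPedi completion within the previous 14 days". Diagnosis is also an input.

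**The concern.** There are two separate problems.

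The first is supply of data. The stated retest interval is one day, but the schedule places entries a week apart. Any pair of entries on adjacent days would have to come from unplanned use of the app.

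The second is fit to the claim. The output is a rule applied to a short-term symptom state. If symptoms change overnight, a correct rule may have to change its output, and the ICC falls. If symptoms hold steady, a faulty rule can repeat its fault, and the ICC stays high. The section names no reference standard for what the system should have delivered, so neither a high nor a low ICC can be read as evidence about correct output.

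At stake is how one implementation result is read. The app advises families directly, and its highest alert prompts a call to the hospital. An ICC published as evidence of appropriate recommendations could reassure or alarm without foundation.

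**Working it through.** The article gives no target ICC, expected ICC or number of retest pairs, so there is no figure to reproduce. Three checks apply.

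**1. Schedule arithmetic.** Inputs: weekly entries for eight weeks, and reminders at 24 h and 48 h (Procedures).

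- Entry days: 0, 7, 14, …, 49. Eight entries give 7 gaps, each of 7 days. If the schedule means nine entries, there are 8 gaps, again of 7 days.
- Suppose each entry may be 0, 1 or 2 days late, in line with the reminders. Shortest gap: 7 + 0 − 2 = 5 days. Longest gap: 7 + 2 − 0 = 9 days.
- A one-day gap between two scheduled entries would need the first to be 6 days late and the second on time (7 − 6 = 1).

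Scheduled one-day pairs: 0 of 7 intervals. The reminders prompt a late entry, not a second one.

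**2. Does the ICC respond to correctness?** For two days per child, the one-way ICC is (MSB − MSW) / (MSB + MSW), where MSB is the between-child and MSW the within-child mean square. Code the three responses 0, 1, 2 and reverse them, so that x becomes 2 − x. Every deviation from a mean changes sign, every square is unchanged, and so MSB, MSW and the ICC are unchanged. This is exact and needs no assumption about the data.

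A simulation shows what the ICC does follow. The inputs are assumptions, not trial figures: one 0–4 item cut from a normal variable at −0.3, 0.4, 1.0 and 1.6; scores 0–1 mapped to response 0, score 2 to response 1, scores 3–4 to response 2; 200,000 pairs.

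| Assumed day-to-day latent correlation | ICC of score | ICC of response, intended mapping | ICC of response, reversed mapping |
|---|---|---|---|
| 0.9 | 0.84 | 0.79 | 0.79 |
| 0.7 | 0.64 | 0.55 | 0.55 |
| 0.5 | 0.44 | 0.37 | 0.37 |
| 0.2 | 0.17 | 0.14 | 0.14 |

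By construction the intended mapping is right for 100% of entries. The reversed mapping is right only where the middle response applies, which is 19% of entries. The ICC moves with symptom stability down the table and is blind to the mapping across it.

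**3. Are the two days replicates?** The algorithms refer to entries within the previous 14 days. A day-2 entry falls inside the window opened by the day-1 entry, so the second output may depend on the first input. The article does not say how the look-back alters the output, so the size and direction of this effect cannot be worked out.

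**The case against.** The strongest reply has four parts.

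- *No scheduled pairs is not the same as no pairs.* A reader might infer that the analysis would have no data at all. The documents do not support that. Nothing says the app blocks extra entries, a 1-week graph view exists, the dashboard sets SSPedi timing, and frequency of app use is itself to be recorded. One-day pairs may occur. It stands, however, that the article does not name them as the source of the ICC, and that they would be unplanned.
- *A retest procedure may be described in the full protocol or analysis plan.* That is possible, and the missing operational detail is not the complaint. What the article does state is a one-day interval beside a weekly schedule. An analysis plan could supply planned pairs only by adding data collection that this schedule does not contain, and it could not turn an ICC into a measure of correctness.
- *One day is a sensible retest interval for this instrument.* The recall periods of adjacent days overlap, and the Background describes symptoms as persistent. This is fair, and supports an ICC as a measure of short-term score stability. It does not support the claim about recommendations. How much symptoms really vary from day to day in this population is not given, which is why the table spans a wide range.
- *The look-back argument is partly conjecture.* A reader might infer that identical scores on two days would properly give different alerts. That is plausible, but the article does not specify it. Only the weaker statement holds: the second output may not be an independent replicate.

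It is also fair that appropriateness and safety are approached by other routes: clinicians ratified the algorithms, alert-related contacts and referrals are audited, and interviews cover safety.

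**Conclusion.** The point holds. As written, the retest interval does not match the schedule (0 of 7 scheduled intervals are one day), and the chosen statistic cannot support the stated claim whatever value it takes. The first part rests on the weekly schedule alone. The second rests on an algebraic identity; the simulated ICCs only illustrate it and do not estimate anything in this trial.

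The consequence is limited. This is a secondary implementation analysis, and neither the primary outcome nor any of the four a priori success criteria depends on it. A reader might also infer that the system's advice is wrong or unsafe; nothing in the article shows that. The finding is that this analysis would not tell us either way. It should be corrected before the result is reported.

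**What to change.** Do not use the consecutive-day ICC as evidence that recommendations are appropriate. Instead:

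1. Re-run the ratified algorithm offline on every logged SSPedi entry, with the 14-day history and diagnosis as inputs. The article collects diagnosis from medical records and says that app data are not linked to them, so diagnosis may have to be joined from study records.
2. Report agreement between expected and delivered alert level and recommendation, and list every discordant red alert. At full completion by 80 children this is 80 × 8 × 15 = 9,600 item-level outputs. That number is a ceiling on the checks available, not a measure of error.
3. Give confidence intervals that allow for clustering within child. An exact binomial interval on 9,600 outputs would treat them as independent. Reporting also the proportion of children with any discordant output gives one unit per child; with 0 of 80 discordant, the exact two-sided 95% upper limit is 1 − 0.025^(1/80) = 0.045.
4. Describe the result as fidelity of the software to the ratified algorithm. It would show 100% agreement even if the rules themselves were poor, so it is not proof of clinical appropriateness. That claim needs an external standard, such as blinded clinician review of a sample with weighted kappa over the three levels.
5. If the ICC is kept, report it only as short-term score stability and state where the consecutive-day pairs come from.

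Cost: a change of wording and a short script. The article already plans to record every app event, so families do nothing more. The possible extra work is the diagnosis linkage and, if chosen, clinician time for the review. No alert threshold or clinical rule changes.
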